**Discussion:**

This is the first double-blind, randomised controlled trial to directly compare the safety and biochemical non-inferiority of glucose-only therapy versus standard insulin–dextrose therapy in the emergency department. By utilising a continuous glucose infusion following a bolus, the protocol aims to sustain endogenous insulin release and optimise intracellular potassium shift while preventing hypoglycaemia. If non-inferiority is demonstrated, this approach could provide a safer alternative in high-acuity or resource-limited clinical settings.

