Most studies in patients without diabetes found reductions in potassium following glucose administration, ranging from 0.15 mmol/L (2.7 mg/dL) to 0.91 mmol/L (16.4 mg/dL). The most robust evidence comes from a small randomised controlled trial by Chothia et al. which found average potassium reductions of 0.5 mmol/L (9 mg/dL) in the glucose-only arm compared to 0.83 mmol/L (15 mg/dL) in the IDT arm [9]. Importantly, the lower potassium reduction was offset by an improved safety profile as no hypoglycaemia occurred in the glucose-only group, compared to 20% in the IDT group. Additional support is provided by the study by DeFronzo et al. which demonstrated a 0.81 mmol/L (14.6 mg/dL) reduction in plasma potassium following a two-hour glucose infusion where blood glucose was maintained at 6.9 mmol/L (124 mg/dL) above baseline in healthy participants [17].

Endogenous insulin production following glucose administration is dose dependent and the hypokalaemic effect is dependent on the insulin concentrations achieved [18–20]. There does, however, appear to be a ceiling to the hypokalaemic effect [17]. Studies measuring insulin levels after glucose administration consistently report lower insulin levels compared to studies examining IDT. Most studies, however, used bolus glucose administration, and we hypothesise that a glucose bolus followed by a continuous infusion will sustain higher insulin levels over time and enhance potassium-lowering efficacy [11]. Since endogenous insulin release may be suppressed by counter-regulatory hormones during critical illness, our study protocol restricts enrollment to hemodynamically stable patients [21].

This trial responds to calls for glucose-only therapy to be included in future clinical trials for non-diabetic patients with hyperkalaemia [10]. The cross-over trial by Chothia et al. provides an important proof of concept but is limited by its small sample size and specific patient population, being restricted to haemodialysis recipients [9]. Our study aims to build on this foundation by enrolling a larger and more diverse ED population and adding nebulized salbutamol to both treatment arms to exploit complementary mechanisms for intracellular potassium shift. Furthermore, in the glucose-only arm, participants receive a two-hour glucose infusion following the initial bolus. This may sustain endogenous insulin release, thereby increasing the total potassium shift.

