### Intervention

Participants will be allocated *via* stratified (potassium <6.5 mmol/L [117 mg/dL] or ≥6.5 mmol/L [117 mg/dL), block randomisation to receive either glucose-only therapy or insulin–dextrose therapy (IDT) in a 1:1 ratio with the use of sequential, opaque, sealed envelopes. Envelopes are opened by members of the research team or clinical pharmacists only after formal participant enrolment is confirmed and documented. Interventions will be prepared by the same staff who open the envelope and away from clinical areas. Study solutions will appear visually identical to ensure blinding of participants and treating clinicians. The study period extends for six hours following randomisation. In eligible participants, treatment commences as soon as possible after enrolment.

In the glucose-only arm, participants will receive 100 mL of 50% dextrose administered over 10 min, followed immediately by 250 mL of 10% dextrose infused over two hours.

In the insulin–dextrose arm, participants will receive 10 units of intravenous insulin (Actrapid) mixed with 50 mL of 50% dextrose and 50 mL of 0.9% sodium chloride (total 100 mL), administered over 10 min, followed by 250 mL of 0.9% sodium chloride infused over two hours.

Infusion bag 1 (100 mL) will be prepared by modifying 0.9% sodium chloride bags according to the assigned intervention. Study labels will be affixed to the front of each bag. Infusion bag 2 (250 mL) will consist of the proprietary product used in each arm without alteration; these bags will be concealed using an opaque black sleeve to mask product identity, with study labels applied to the exterior.

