## Statistical considerations

The target sample size for this study is 95 enrolments (approximately 48 per treatment arm). This sample size was primarily determined to provide 80% power to detect a statistically significant difference in the incidence of hypoglycaemia, assuming an incidence of 17% in the IDT group and 0% in the glucose-only group, using a two-sided significance level (α) of 0.05.

To account for repeat enrolments (maximum of two per participant), a design effect of 1.1 was applied. This was derived from an assumed intra-class correlation coefficient (ICC) of 0.3 and an average of 1.2 enrolments per participant. The ICC was conservatively selected to reflect potential within-subject correlation in hypoglycaemia risk. The final figure of 95 enrolments includes a 10% buffer to account for attrition or missing data (e.g. missed blood glucose measurements or haemolysed potassium samples).

This sample size also provides sufficient power for the primary non-inferiority objective serum potassium reduction at two hours. With a non-inferiority margin of −0.5 mmol/L (–9 mg/dL), an assumed true mean difference of 0.0 mmol/L and a standard deviation of 0.8 mmol/L (14.4 mg/dL), a minimum of 82 enrolments is required to achieve 80% power (α = 0.025, one-sided). Thus, the planned recruitment of 95 enrolments ensures the study is adequately powered for both primary endpoints.

All analyses will adhere to a modified intention-to-treat (mITT) principle, including participants who are randomised, receive the assigned intervention, and have at least one post-baseline potassium and BGL measurement. For participants commencing dialysis within the 6-hour observation period, data up to the point of dialysis initiation will be included. Per-protocol analyses will be undertaken as sensitivity analyses to assess potential bias arising from treatment cross-over (patients in the glucose only group receiving insulin).

For the primary safety outcome (hypoglycaemia incidence), proportions will be summarised by treatment group, and the between-group difference will be reported with 95% confidence intervals (CI). Groups will be compared using Fisher’s exact test. If clustering due to repeat enrolments is evident, a generalised linear model with a binomial error structure and robust standard errors adjusted for clustering will be used.

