## Potential impact and dissemination

The primary potential impact of this study is to determine whether glucose-only therapy can serve as an insulin-sparing treatment option for hyperkalaemia in patients without diabetes. By eliminating the need for exogenous insulin in this population, glucose-only therapy removes the risk of iatrogenic hypoglycaemia—a complication that remains a major safety concern with standard insulin–dextrose therapy, particularly in patients without diabetes. If demonstrated to be both safe and biochemically effective, this approach could potentially improve patient safety and reshape current ED practice.

Beyond individual patient outcomes, the adoption of glucose-only therapy could deliver broader operational advantages. It does not require refrigeration or intensive post-administration glucose monitoring, enhancing its practicality in busy ED and improving workflow efficiency. These features also make it well suited to pre-hospital or resource-limited environments, where access to insulin, refrigeration, or frequent glucose monitoring may be constrained. These principles may have relevance in battlefield or remote settings, where prolonged evacuation and logistical constraints compound the risk of hyperkalaemia in casualties with crush injury or ischaemia-reperfusion injury following tourniquet release [23]. However, the substantial counter-regulatory hormone response to haemorrhagic shock may significantly impair endogenous insulin secretion, undermining the core mechanism and so further research in this population is therefore required before extrapolation can be justified [21]. Regardless of results, findings will be disseminated in peer-reviewed journals and at national and international conferences.

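### The claim that 95 enrolments power both primary endpoints sets an uninflated 82 against an inflated 95, rests on an unsupported zero difference, and does not match the planned Fisher's exact test

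*Protocol article*

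**What the plan says.** All sizing statements are in the Statistical considerations section of the protocol article.

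- **Total.** "The target sample size for this study is 95 enrolments (approximately 48 per treatment arm"). It is sized primarily on hypoglycaemia, 17% versus 0%, with 80% power at two-sided 0.05.
- **Inflation.** For repeat enrolments, "a design effect of 1.1 was applied", from an ICC of 0.3 and 1.2 enrolments per participant. The ICC is justified by correlation in hypoglycaemia risk. A 10% buffer is also included, and haemolysed potassium samples are one of its stated reasons.
- **Non-inferiority.** With a margin of 0.5 mmol/L, SD 0.8, true difference 0.0 and one-sided 0.025, "a minimum of 82 enrolments is required to achieve 80% power". No inflation is mentioned.
- **Conclusion.** "Thus, the planned recruitment of 95 enrolments ensures the study is adequately powered for both primary endpoints".
- **Safety test.** Fisher's exact test, or a binomial model with cluster-robust standard errors if clustering is evident.

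The Introduction reports that the trial it regards as the most robust evidence "found average potassium reductions of 0.5 mmol/L (9 mg/dL) in the glucose-only arm compared to 0.83 mmol/L (15 mg/dL) in the IDT arm". The Abstract's Discussion paragraph says "If non-inferiority is demonstrated, this approach could provide a safer alternative". The Potential impact and dissemination section sets a wider condition: "If demonstrated to be both safe and biochemically effective".

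**The concern.** The conclusion is unqualified and covers both primaries, yet three things beneath it do not line up. The 82 and the 95 are on different bases. The 82 needs glucose-only to be fully equal to insulin–dextrose, with no reason given at that point and no sensitivity range. The formula behind the 95 is not the test that will be run.

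What is at stake is how the result will be read. If glucose-only is even modestly worse, a missed non-inferiority margin is a likely result that settles little. A reader who relied on the power statement would take it for a firm negative. The Trial feasibility section says the target is close to all eligible presentations expected over two years, so a shortfall cannot easily be made up later.

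**Working it through.** **Inputs** (Statistical considerations unless noted): 95 enrolments; 1:1 allocation (Intervention section); margin 0.5, SD 0.8, true difference 0.0, one-sided 0.025; 17% versus 0%, two-sided 0.05; design effect 1.1; loss 10%; deficit in the cited trial 0.83 − 0.50 = 0.33 mmol/L (Introduction).

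**1. Reproduce the 82.** n per arm = 2 × (0.8/0.5)² × (1.96 + 0.8416)² = 40.2, so 41 per arm and 82 in total. This is the raw size, with no design effect and no attrition.

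**2. Reproduce the 95.** Unpooled normal formula: n per arm = (1.96 + 0.8416)² × (0.17 × 0.83)/0.17² = 38.3, so 39 per arm and 78 in total. Then 78 × 1.1/0.9 = 95.3. The 95 is therefore inflated.

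**3. Put the 82 on the same basis.**

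- Design effect 1.1 and 10% loss: 82 × 1.1/0.9 = 100.2, so 101. With the buffer as a multiplier, 82 × 1.1 × 1.1 = 99.2, so 100.
- Design effect before rounding, 1 + (1.2 − 1) × 0.3 = 1.06: 82 × 1.06/0.9 = 96.6, so 97.
- Loss only: 82/0.9 = 91.1, so 92, which 95 covers.

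**4. Non-inferiority power with 95 enrolled.** Power = Φ((0.5 − d)/(0.8 × √(2/n)) − 1.96), where d is the true deficit of glucose-only and n the effective number per arm. With 10% loss and design effect 1.1, n = 95 × 0.9/1.1/2 = 38.86.

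| True deficit (mmol/L) | All 95 analysed (n = 47.5) | 10% loss (n = 42.75) | 10% loss, DE 1.1 (n = 38.86) | Same, t-based |
|---|---|---|---|---|
| 0.0 | 86% | 82% | 79% | 78% |
| 0.1 | 68% | 64% | 60% | 59% |
| 0.2 | 45% | 41% | 38% | 37% |
| 0.33 | 18% | 16% | 15% | 15% |

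With 10% loss and the unrounded 1.06, power at zero difference is 80.1%. For 80% power at a deficit of 0.33, about 696 analysed enrolments would be needed.

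**5. Safety primary under Fisher's exact test** (exact enumeration, 17% versus 0%).

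| IDT / glucose | Fisher power | Basis |
|---|---|---|
| 39 / 39 | 67% | 10% loss and DE 1.1 |
| 38 / 39 | 80% | same, glucose arm one larger |
| 39 / 40 | 82% | same, glucose arm one larger |
| 43 / 43 | 76% | 10% loss, no DE |
| 42 / 43 | 86% | 10% loss, glucose arm one larger |
| 48 / 47 | 85% | no loss |
| 47 / 48 | 92% | no loss |

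The jumps come from the discreteness of the test. At 39/39, five events against none gives p = 0.0545 and just misses, so six are needed. With one more participant in the glucose arm, five are enough.

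**6. Both primaries together, if that were required.** Taking the endpoints as independent, joint power is the product of the two: 0.788 × 0.671 = 53% at 39/39; 0.783 × 0.798 = 62% at 38/39; 0.826 × 0.762 = 63% at 43/43; 0.821 × 0.864 = 71% at 42/43; 0.861 × 0.920 = 79% at 47/48. The range is about 53–79%, all at a true potassium difference of 0.0.

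**The case against.** **The omitted inflation is minor.** This stands. Attrition alone fits within 95, and with the unrounded design effect power is still 80.1%. The ICC was chosen for hypoglycaemia, so carrying it over to potassium change is an assumption. Taken alone, this part would not make the claim of adequate power wrong.

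**The cited trial does not contradict a zero difference.** A reader might infer that it does, but the documents do not go that far. The Introduction describes a small cross-over trial in haemodialysis patients, and says the present trial adds a two-hour infusion to the bolus, salbutamol in both arms and a broader population. It puts forward the infusion as a reason for a better potassium response. That is a hypothesis, however, and nothing shows that it would recover the whole 0.33 mmol/L. The same section notes lower insulin levels after glucose than in studies of insulin–dextrose. So the zero is unsupported, not refuted.

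**Joint power of 53% is not a fact about this trial.** A reader might infer that both primaries must succeed and that the chance is close to even. No passage sets such a rule: the power sentence can be read endpoint by endpoint, and the impact section is conditional prose. The 53% also needs an exact 39/39 split, independence, full loss and the rounded design effect. It pairs a clustering allowance with Fisher's test, which the plan replaces if clustering is evident. It lies near the bottom of the range.

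**Power might be recovered by changing the analysis**, for example by baseline adjustment. The documents give no baseline correlation, and the plan rules out covariate adjustment, so no gain can be stated.

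**Conclusion.** The concern holds in a limited form and warrants correction. The 82 and the 95 are not on the same basis. Corrected, non-inferiority power at zero difference is about 78–80% with design effect and loss, or 82% with loss only, which is a shortfall of at most about two points.

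The weight lies elsewhere. The zero difference is unjustified where it is used, and power falls to 59–68%, 37–45% and 15–18% at deficits of 0.1, 0.2 and 0.33 mmol/L. For the safety primary, Fisher's test gives about 67% at an effective 39/39 and 76% at 43/43, but about 80–86% when the glucose arm is one larger and at least 85% if all 95 are analysed. Adequate power for both endpoints is therefore possible but not ensured.

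These figures take the stated SD of 0.8 and the 17% versus 0% rates as given. They treat clustering as a simple reduction in effective size, with the hypoglycaemia ICC applied to potassium where a design effect is used. The upper end of each range at a non-zero deficit assumes that all 95 are analysed.

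**What to change.** 1. Replace the sentence that 95 ensures adequate power for both primaries. Suggested text: *With 95 enrolments, after design effect and attrition, non-inferiority power is about 78–80% if the true difference is 0.0 mmol/L (82% with attrition only). Depending on losses and clustering it is 59–68%, 37–45% and 15–18% if glucose-only is 0.1, 0.2 or 0.33 mmol/L worse. Fisher's exact test for 17% versus 0% has about 67% power at an effective 39 per arm and 76% at 43 per arm, or about 80–86% if the glucose arm is one larger.*
2. Give the reason for assuming 0.0 beside the assumption, and say whether the design effect is meant to apply to potassium.
3. If support for glucose-only therapy needs both primaries, say so and report joint power as a range of about 53–79%, assuming independence and a zero potassium difference.
4. Bring the Abstract's Discussion paragraph into line with the impact section, so that a claim of greater safety rests on the hypoglycaemia primary and not on non-inferiority alone.

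The cost is a few rewritten sentences and a less favourable stated power. No additional patients and no change of analysis are needed.

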### Outcomes

The primary safety outcome is the incidence of hypoglycaemia (blood glucose <3.9 mmol/L (70 mg/dL), within 6 h post-treatment). Blood glucose is measured using validated bedside point-of-care glucometers. The primary non-inferiority outcome is the mean change in serum potassium (mmol/L) from baseline to 2 h post-treatment. Note that if a patient is enrolled based on a blood gas result due to clinical urgency, only the contemporaneous serum sample will be used for analysis. Secondary outcomes are severity of hypoglycaemia (ADA criteria); incidence of infusion-related complications including thrombophlebitis and extravasation; proportion of participants requiring rescue insulin therapy within 6 h post-treatment; mean change in serum potassium from baseline at 1 h and 4–6 h post-treatment; proportion of participants achieving a clinically significant potassium reduction (≥0.5 mmol/L [9 mg/dL] within 2 h); presence and resolution of hyperkalaemic ECG changes; serum insulin and C-peptide concentrations at baseline, 1 h, and 2 h post-treatment.

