### Trial feasibility, challenges and limitations

Recruitment and enrolment in this study are inherently complex due to the time-critical nature of hyperkalaemia management. Clinicians must rapidly identify eligible patients and navigate a narrow treatment window while ensuring patients have adequate opportunity to provide informed consent—a task made difficult by the high-acuity ED environment. These clinical challenges are further compounded by the pathophysiological characteristics of this cohort; specifically, patients with end-stage renal disease (ESRD) often present with difficult venous access. The subsequent need for reliable, large-bore intravenous access to safely administer hypertonic glucose infusions can introduce significant delays to the enrolment process.

Beyond these clinical hurdles, the emergency setting is characterized by a pressured workload and rapid patient movement. Frequent transfers to inpatient wards or dialysis units act as a barrier to complete data collection, as maintaining the protocol’s structured follow-up and timely blood sampling becomes logistically difficult across different clinical teams and locations. Furthermore, study blinding and infusion preparation rely heavily on clinical pharmacists, effectively limiting recruitment to the hours of pharmacist availability (07:00–23:00). As a single-site RCT with a target sample size that closely approximates the expected number of eligible presentations over two years, there is limited tolerance for missed enrolments, necessitating sustained vigilance.

To mitigate these pressures, a comprehensive education and engagement campaign was undertaken prior to trial commencement. Research staff presented the protocol at departmental meetings, registrar teaching, and nursing in-services to ensure familiarity with eligibility and referral processes. Crucially, this effort is underpinned by a robust departmental research culture fostered by the successful delivery of previous randomised trials. The sustained support of the senior leadership team has been instrumental in integrating research into standard clinical workflows, ensuring that trial activity is viewed as a core component of departmental practice rather than an optional addition to a busy shift.

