For the primary efficacy outcome (change in serum potassium at two hours), mean (SD) reductions in each group and the between-group mean difference (95% CI) will be reported. Non-inferiority will be concluded if the lower bound of the 95% CI is greater than −0.5 mmol/L (–9 mg/dL).

Secondary outcomes will be summarised descriptively by treatment group. To compare groups, general linear models will be calculated with an identity or binomial error structure for continuous or categorical outcomes. Group differences will be reported as mean differences (continuous) and risk differences or risk ratios (categorical) with 95% CIs. Repeated measures data will be analysed using linear mixed-effects models, which account for within-subject correlation and accommodate missing data.

Missing data will be managed based on the extent of data loss. If missingness is minimal (<5%), cases with missing data will be excluded from analysis. Potassium results from haemolysed samples will be counted as missing data. Mixed-effects modelling will allow the inclusion of all available data, mitigating bias related to incomplete measurements.

No adjustment for baseline covariates is planned, as randomisation is expected to achieve balance between treatment groups. A two-sided p-value of <0.05 will be considered statistically significant. All analyses will be performed using an appropriate statistical software package.

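### The single mITT set makes the hypoglycaemia primary depend on a potassium result and on receipt of the assigned bag, so it can exclude a recorded hypoglycaemia event

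*Protocol article*

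**What the plan says.** All references are to the protocol article.

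- **Scope of the set** (Statistical considerations): "All analyses will adhere to a modified intention-to-treat (mITT) principle". Both primaries are covered, and no separate safety set is named.
- **Membership** (same section): participants must be randomised, "receive the assigned intervention, and have at least one post-baseline potassium and BGL measurement".
- **Safety primary** (Outcomes): "The primary safety outcome is the incidence of hypoglycaemia (blood glucose <3.9 mmol/L (70 mg/dL), within 6 h post-treatment". It is compared between arms as a simple proportion with Fisher's exact test.
- **Potassium validity** (Statistical considerations): "Potassium results from haemolysed samples will be counted as missing data".
- **Sampling schedule** (Table 2): after baseline, glucose is due hourly from hour 1 to hour 6. Serum potassium is due at hours 1 and 2 and once between 4 and 6 hours.
- **Expected losses** (Trial feasibility, challenges and limitations): "Frequent transfers to inpatient wards or dialysis units act as a barrier to complete data collection".
- **Dialysis and missing data** (Statistical considerations): participants who start dialysis within six hours contribute their data up to that point. If less than 5% is missing, the affected cases are excluded. Mixed models are to use all available data. Per-protocol analyses are planned separately, as sensitivity analyses.

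**The concern.** Two membership conditions do not belong in the primary set for a glucose safety endpoint.

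First, a potassium result decides whether a glucose event counts. Someone who received study treatment and had a documented low glucose has a known outcome. The absence of a different assay is no reason to set that outcome aside.

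Second, requiring receipt of the assigned intervention puts a per-protocol condition into the primary set. A participant given the wrong bag disappears from the comparison instead of being kept in the randomised arm.

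Both conditions are met or failed after randomisation. The safety primary rests on few events, almost all expected in the insulin–dextrose (IDT) arm, so each excluded event carries weight. If missing potassium is linked to early dialysis or transfer, and these depend on the potassium response, the losses could also differ by arm. The article gives no figure for that.

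A related loose end is that one glucose reading out of six admits a participant to a six-hour incidence, and the text does not settle how an incomplete, event-free series is counted.

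**Working it through.** **Inputs from Statistical considerations.** "assuming an incidence of 17% in the IDT group and 0% in the glucose-only group"; "using a two-sided significance level (α) of 0.05"; 80% power; design effect 1.1; 10% buffer; 95 enrolments, about 48 per arm.

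**1. The plan's own figure.** With unpooled variance, n per arm = (1.960 + 0.842)² × (0.17 × 0.83) / 0.17² = 7.849 × 0.1411 / 0.0289 = 38.3, so 39 per arm and 78 in total. Then 78 × 1.1 = 85.8, and 85.8 × 1.1 = 94.4 (or 85.8 / 0.9 = 95.3). The stated 95 is reproduced and is not in dispute.

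**2. How few events carry the result.** Expected IDT events are 0.17 × 48 = 8.2. With 0 events in the other arm, two-sided Fisher needs at least 6 IDT events at 48 versus 47. The probability of 6 or more from a binomial with n = 48 and rate 0.17 is 0.85, which is the power under full observation.

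**3. Effect of excluding one participant with an event.** The excluded participant leaves the numerator and the denominator.

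| Before | p | After | p |
|---|---|---|---|
| 8/48 v 0/47 | 0.006 | 7/47 v 0/47 | 0.012 |
| 6/48 v 0/47 | 0.026 | 5/47 v 0/47 | 0.056 |
| 6/48 v 0/48 | 0.026 | 5/47 v 0/48 | 0.026 |
| 6/43 v 0/43 | 0.026 | 5/42 v 0/43 | 0.026 |

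One exclusion therefore changes the conclusion only near the boundary, and only at some arm sizes.

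**4. How likely is it that no potassium is usable?** The article gives no rate. If haemolysis struck each sample independently with an assumed probability of 5%, 10% or 20%, all three would be lost with probability 0.05³ = 0.01%, 0.1³ = 0.1% or 0.2³ = 0.8%. Haemolysis alone is thus an unlikely route. Missed draws after early transfer or dialysis are more plausible, at an unknown rate.

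**5. Incomplete glucose series (illustration on assumed figures).** Suppose a share q of IDT participants were part-observed, half their risk fell in the observed hours, and the rest were counted as event-free. The observed rate is then 0.17 × (1 − q/2). For q = 10%, 20% and 30% this is 16.2%, 15.3% and 14.5%. Fisher power at 48 versus 47 becomes 0.81, 0.76 and 0.71, against 0.85 with full observation. The article states neither q nor this counting rule.

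**The case against.** The strongest defence is that the membership rule will rarely bite, and most of it stands.

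- **Any one usable potassium keeps the participant in.** Missing the two-hour value, or having one haemolysed sample, removes nobody.
- **Wrong-bag errors should be rare.** The person who opens the envelope also prepares the infusion (Intervention). The cross-over that the article does anticipate, insulin given in the glucose-only arm, is left to the per-protocol sensitivity analyses and is not a reason for exclusion from the mITT set.
- **Loss unrelated to glucose does not bias incidence.** It removes events and non-events in proportion and costs precision only. Bias needs a link between missing potassium and outcome or arm, which is possible but unquantified.

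Two stronger readings are tempting and are not supported.

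A reader might infer that part-observed participants are counted as free of hypoglycaemia. The one-reading threshold, the cut at dialysis and the simple proportion make this natural, but no sentence says so, and the rule for missingness below 5% points to exclusion. Detail of this kind may also sit in an analysis plan that is not shown.

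A reader might also take the 10% buffer as the loss caused by the potassium condition, which at 43 per arm would lower Fisher power from 0.85 to 0.76. The buffer covers all attrition and missing data, including missed glucose readings, so the article gives no basis for charging it to this condition.

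None of this defends the two conditions themselves. They are stated rules that serve no purpose for the safety primary.

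**Conclusion.** The point holds as a defect in a stated rule. Followed literally, the single set can exclude an observed hypoglycaemia event for want of a potassium result, and it excludes wrong-bag participants instead of analysing them as randomised.

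The likely size is small. At about the expected count, one lost event does not alter the conclusion. A reversal needs a result near the boundary and particular arm sizes. These p values assume no events in the glucose-only arm, as the sample-size calculation does, and treat enrolments as independent, as Fisher's test does. The number of participants affected cannot be derived from the article.

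The handling of incomplete, event-free glucose series is unsettled rather than wrong; the power figures for it are illustrations on assumed inputs. The change is worth making because it costs only wording and gives a cleaner safety comparison.

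**What to change.** Replace the single set with endpoint-specific sets, each analysed by randomised arm.

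- **Safety primary:** all randomised participants in whom study bag 1 was started and who have any post-baseline glucose reading, with no potassium requirement. Any reading below 3.9 mmol/L within six hours counts as an event.
- **Potassium primary:** all randomised participants in whom bag 1 was started, with a baseline serum potassium and any valid post-baseline serum potassium.
- **Wording:** delete 'assigned' from the intervention criterion. The planned per-protocol sensitivity analyses remain the place to examine departures from allocation.
- **Incomplete, event-free glucose series:** state how they enter the proportion, and add a sensitivity range for the risk difference from the best-case to the worst-case assignment of the unobserved outcomes.

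The cost is a change of text in the protocol and analysis plan, and slightly different denominators for the two primaries. No new data are needed and 95 enrolments stands. The trial has already started, so the change should be dated and made before any unblinded data are seen.
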